|                                                | Blood – HIV (with counseling), HBsAg, chemistries,
fasting lipids, CBC            | ✓                        |                                  |         |                                         |                       |                                |                      |                             |                                |                                             |                                 |
|                                                | Blood – P4                                                                           |                          | ✓                    |         |                                         |                       |                                |                      |                             |                                |                                             |                                 |
|                                                | Pelvic – Bimanual, GC, CT, trich, pH, Nugent Score
If indicated: Pap and wet prep | ✓                        | (✓)                              |         |                                         |                       |                                |                      |                             |                                |                                             |                                 |
| Randomize and dispense assigned IVR; weigh IVR |                                                                                      |                          |                                  |         | ✓                                       |                       |                                |                      |                             |                                |                                             |                                 |
| Directed Physical Exam                         |                                                                                      |                          |                                  | (✓)     | (✓)                                     |                       | (✓)                            | (✓)                  | (✓)                         | (✓)                            | (✓)                                         |                                 |

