| Visit #                                                            |                                                                   |                                                   | Visit 1                  | Visit 2                          | Visit 3 | Visit 4 
(IVR insertion) |                                  | Visit 5
(24 h p
Visit 4) | Visit 6  | Visit 7
(IVR
removal) | Visit 8
(24 h p
Visit 7) | Visit 9 
(72 h p
Visit 7) | Follow-
up call /
contact |  |
|                                                                    |                                                                   |                                                   |                          |                                  |         | Pre-
insertion                       | Post-insertion                   |                                |                      |                             |                                |                                             |                                 |  |
| Pelvic exam
and genital
samples                              | Pelvic exam                                                       |                                                   |                          |                                  | ✓       | ✓                                       | ✓
(1,2,4,or 8 h)  | ✓                              | ✓                    | ✓                           | ✓                              | ✓                                           |                                 |  |
|                                                                    | If indicated: wet prep & pH                                       |                                                   |                          |                                  | (✓)     | (✓)                                     |                                  | (✓)                            | (✓)                  | (✓)                         | (✓)                            |                                             |                                 |  |

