### 9.1. Visit 1: Screening/Enrollment

Visit 1 should be scheduled at a time when the volunteer does not expect to be menstruating. Volunteers will be consented at Visit 1 and undergo procedures to confirm they are eligible to continue in the study.

- The study and informed consent form will be reviewed and all volunteer questions will be answered. If the volunteer wishes to participate and meets preliminary study criteria, she will be asked to review and sign an informed consent form. The Principal Investigator (PI) or designee will sign the form and provide a copy to the participant. Permission will be requested as part of the informed consent process for storage of the biologic samples obtained during the study for results confirmation and/or possible future testing will be explained, as allowed by the site.
- An interview will be conducted to obtain medical history and demographic information.
- Height, weight, and blood pressure will be measured.
- Directed physical exam will be performed if history is significant for medical condition.
- A urine specimen will be obtained for a urine pregnancy test to confirm that the participant is not pregnant and to perform a dipstick urinalysis if symptomatic for infection (specimen will be clean-catch if the participant is symptomatic, and urine microscopy and culture will be performed as clinically indicated).
- An HIV test will be performed, along with appropriate counseling and/or referral.
- Blood samples will be collected for CBC, serum chemistries, fasting lipids, and HBsAg testing.
- A pelvic examination (including bimanual examination) will be performed with findings managed as outlined in [Table 12: Safety Management Plan for Local Toxicity](#) and below:
  - Sample for wet mount will be taken during the pelvic exam if the participant is symptomatic for vulvovaginal candidiasis or BV
  - Sample for *Trichomonas vaginalis* will be taken
  - Gram stain and pH will be performed at the site to assess for BV
  - Specimens for GC and CT will be collected
  - A Pap smear will be performed, as consistent with current practice guidelines
- Symptomatic urinary tract infection (UTI) and yeast infections will be treated, preferably with oral medication. If symptomatic trichomoniasis or BV is diagnosed, the participant will be treated and will not be allowed to continue in the study.

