## 9.7. Visit 7: IVR Removal and Sample Collection

Visit 7 should occur 8-10 days after Visit 6 (or repeat Visit 6) to allow for the maximum number of days of IVR use in this menstrual cycle while ensuring that participants are seen for final genital sampling before their next menses begins.

- The guidebook, including reported AEs, CTs and the menses diary, will be reviewed.
- The study staff will ask the participant if she followed the instructions regarding vaginal products and vaginal activity. If she did not, she will be reminded of protocol requirements and the visit will continue.
- The participant will complete an acceptability questionnaire.
- A urine specimen will be obtained for a urine pregnancy test.
- A directed physical exam, dipstick urinalysis (and possibly microscopy/cultures) and/or wet mount/pH will be performed, if indicated. If a symptomatic infection is diagnosed, study procedures will continue per investigator discretion and the participant will be treated after completion of the visit procedures.
- Blood will be drawn for TFV and TFV-DP PK, LNG/SHBG PK/PD, CBC, serum chemistry, fasting lipids, and P4.
- A pelvic exam will be performed and the following procedures will be completed in the order listed. Findings will be managed as outlined in [Table 12: Safety Management Plan for Local Toxicity](#).
  - The biopsy sites from previous sampling will be assessed. Subsequent procedures will be done at the investigator's discretion.
  - Collection of vaginal aspirate for TFV PK.
  - Preparation of vaginal swabs for TFV PK, TFV PD, to test for microflora, and semen biomarkers as outlined in the study manual.
  - Collection of CVL for safety and TFV PD.
  - Naked eye/colposcopic examination.
  - Collection of cervical mucus for LNG PK.
  - Transvaginal ultrasound to assess endometrial thickness.
  - The IVR will be removed.
  - Collection and processing of one endometrial biopsy (EVMS only) for LNG PD as outlined in the study manual.
  - Collection and processing of up to three biopsies (up to five at EVMS) for safety and TFV and TFV-DP PK, as outlined in the study manual.
  - Appropriate post-biopsy instructions will be discussed with the participant.
- Post-removal ring procedures will be immediately carried out as outlined in the study manual.
- The participant will be given applicable reminders as described in Visit 4.

- Visit 8 will be scheduled to allow for sample collection 24 hours after IVR removal.

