| 
Epithelial findings:
 
 
Erythema, edema, petechiae, ecchymoses (epithelium intact by definition) – includes cervicitis
 
Peeling (superficial epithelial disruption, by definition)
 
Ulcers, abrasions, lacerations with superficial or deep epithelial disruption
 
 | 
If an infection is suspected (e.g., due to erythema, vesicles, concomitant discharge, etc.):
 
A wet prep with KOH and pH, NAAT for GC/CT, and other tests may be done as indicated.
 
 
If candidiasis is diagnosed at Visit 3, the participant may be treated and Visit 2 and 3 rescheduled.
 
If candidiasis is diagnosed at Visit 4, the participant may be treated and Visit 4 rescheduled on cycle day 7 of the next cycle.
 
If candidiasis is diagnosed at Visit 5-8, the participant may be treated and the visit will continue.
 
If trichomoniasis, BV, or herpes simplex is diagnosed at Visit 3-6, the participant should be treated and discontinued.
 
If trichomoniasis, BV, or herpes simplex is diagnosed at Visit 7-8, the participant should be treated and the visit will continue.
 
 
If the finding is bleeding (which makes it deep epithelial disruption by definition), it should be managed as described under "Vaginal bleeding," above.
 
For all findings: If the area is small (less than approximately 3mm at the widest point), samples may be collected or the visit may be rescheduled, per investigator discretion. If the finding is >3 mm, consideration should be given to stopping product use and seeing the participant in unscheduled visits until the finding is resolved or resolving.
 |

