**Table 13: Safety: Genital Assessments**

|                                                                                             | Visit 3 | Visit 4                   |                                      | Visit 5 | Visit 6 | Visit 7 | Visit 8 |
|---------------------------------------------------------------------------------------------|---------|---------------------------|--------------------------------------|---------|---------|---------|---------|
|                                                                                             |         | Pre-insertion
Baseline | Post-insertion
(at assigned time) |         |         |         |         |
| CVL: soluble markers of mucosal immunity                                                    |         | ✓                         |                                      |         |         | ✓       |         |
| Genital Tissue: histology /immune cell activation                                           | ✓       |                           |                                      |         |         | ✓       |         |
| Genital Tissue: markers of mucosal alteration/ epithelial integrity (EVMS only)             | ✓       |                           |                                      |         |         | ✓       |         |
| Swabs: Microflora                                                               |         | ✓                         |                                      |         |         | ✓       |         |
| Microbial growth on swabs obtained from returned IVRs and microbial levels in returned IVRs |         |                           |                                      |         |         | ✓       |         |

 Includes: Semi-quantitative culture; Quantitative PCR (Copan Swab); Nugent Score (Gram Stain)

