## **14.6. Evaluation of Primary Objectives**

### **Genital and Systemic Safety**

Only treatment-emergent AEs, defined as an AE with onset on or after insertion of IVR, will be included in the analysis; AEs reported on CRFs with onset prior to insertion will be listed. AEs will be summarized separately by treatment group based on MedDRA Preferred Term and System/Organ Class. The number of subjects reporting at least one episode of a given AE category (Preferred Term) as well as number of episodes will be summarized and listed. SAEs, if any, will be identified.

Other than AEs, genital safety endpoints will be summarized separately by treatment group and time of measurement.

Treatment effects on serum chemistries, lipids, CBC, pH, and Nugent score will be evaluated clinically from shift tables reflecting change from baseline based on categories to be developed by the CONRAD Study Clinician and described in the SAP (e.g. Normal→ Abnormal/High [e.g., serum chemistries, lipids, or CBC; Normal→ Intermediate → BV [Nugent score]). Shift tables will be created for each follow-up visit at which measurements were obtained. In addition, changes in pelvic examination results immediately before vs. immediately after IVR insertion at Visit 4 will be listed.

Changes in soluble markers of innate mucosal immunity and inflammatory response in CVL, HIV-1 target immune cell phenotypes and activation/proliferation markers, and cervicovaginal epithelial histology will be evaluated clinically from descriptive statistics by treatment group and time point and supplementary graphical displays (e.g., box-plots). Statistical models comparing treatment groups on these endpoints may be addressed in the SAP.

Separate box-plots for immune markers measured in the presence of semen (as determined by the semen biomarkers) vs. those from the same treatment group and sampling time point without the presence of semen will be created, if necessary, to assist with interpretation of these markers.

Non-iatrogenic colposcopy findings will be described based on characteristics at the first observation, though characteristics at all observations will be listed. Development of ulcerations, abrasions, edema, and other findings will be based on diagnoses made by site colposcopists.

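### Section 14.6 plans to judge treatment effects on vaginal pH, but no pH reading is scheduled for all women after Visit 1

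*Protocol*

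**What the plan says.** Under the primary objective, Section 14.6 states: "Treatment effects on serum chemistries, lipids, CBC, pH, and Nugent score will be evaluated clinically from shift tables reflecting change from baseline". It adds: "Shift tables will be created for each follow-up visit at which measurements were obtained". Table 6 places pH among the primary-safety vaginal swab tests, next to culture, PCR and Nugent score, with no condition and no visit.

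The collection side reads differently.

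- **Visit 1.** pH is required of every woman. The Table 3 screening row has "Pelvic – Bimanual, GC, CT, trich, pH, Nugent Score", and Section 9.1 has "Gram stain and pH will be performed at the site to assess for BV".
- **Later visits.** The Table 3 row is "If indicated: wet prep & pH", with bracketed ticks at Visit 3, Visit 4 pre-insertion and Visits 5 to 8. The text for Visit 7, the end of ring use, says "and/or wet mount/pH will be performed, if indicated". Sections 9.2 to 9.9 carry the same condition for the other visits.
- **Findings on examination.** Where infection is suspected, Table 12 says "A wet prep with KOH and pH, NAAT for GC/CT, and other tests may be done as indicated". For vaginal discharge, the same table says that a pH should be done.
- **Routine swabs at Visits 4 and 7.** The Table 13 footnote defines the set: "Includes: Semi-quantitative culture; Quantitative PCR (Copan Swab); Nugent Score (Gram Stain". pH is not in it.

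**The concern.** A shift table needs a baseline and a follow-up value from the same woman, in a set of women not chosen by what happened after randomization. For pH the protocol secures the first but not the second. Whether a woman has a follow-up pH depends on symptoms, examination findings or discharge after the ring is in place. The ring may affect any of these.

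The number of women per arm in the table is then itself a result of treatment, and randomization no longer protects the comparison between arms. A difference in the pH table could reflect who was tested rather than what the ring did. So could the absence of one.

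The SAP cannot repair this. It can define categories and windows, but it cannot create readings that the schedule did not require.

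**Working it through.** No figure in the protocol can be reproduced here. Section 14.1 bases the sample size on feasibility, and no testing rate is given. The check sets the analysis text against the schedule.

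**Step 1. Readings required of every woman, for each variable named in the Section 14.6 sentence.**

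| Variable | Before insertion | After insertion | Source |
|---|---|---|---|
| Chemistries, lipids, CBC | Visit 1 | Visit 7 | Table 3; Section 12.2.3.1 |
| Nugent score | Visits 1 and 4 | Visit 7 | Tables 3 and 13 |
| pH | Visit 1 | none | Tables 3 and 13; Section 9 |

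pH is the only variable without an unconditional post-insertion value.

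**Step 2. Does any other text supply the missing reading?** Table 6 is the only candidate. It assigns no visit, so by itself it schedules nothing. It does show that pH was meant as a safety measurement, and it conflicts with Table 3, the Table 13 footnote and Section 9.

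**Step 3. Which value becomes the baseline?** Section 14.3 takes the last non-missing value before randomization and insertion. For most women that is Visit 1. For a woman tested for cause at Visit 2, 3 or 4, the for-cause value replaces it. Section 9.1 allows up to eight weeks between Visits 1 and 2 before screening is repeated, and Table 4 puts Visit 2 about 14 days before insertion. A Visit 1 baseline can therefore be about 56 + 14 = 70 days old at insertion, and older if Visit 4 falls in the second cycle. The baseline column thus mixes routine and for-cause values.

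**Step 4. Which follow-up tables result?** Conditional testing is allowed at Visits 5 to 8, and also at Visit 9 by Section 9.9, although Table 3 has no tick there. The sentence on follow-up visits could therefore produce several sparse tables, each holding a different selected group. Sections 9.5 and 9.6 and Table 12 also have women with BV or trichomoniasis at Visits 5 and 6 discontinued. Some women tested before Visit 7 would then have no scheduled end-of-use value.

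**Step 5. Illustration of size.** Inputs are 50 completers (Section 7.3) and 2:2:1 allocation (Section 7.4).

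- Full collection: 50 × 2/5 = 20, 50 × 2/5 = 20 and 50 × 1/5 = 10 women.
- Assumed 10% with an indication at Visit 7: 2, 2 and 1 women.
- Assumed 30%: 6, 6 and 3 women.

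The 10% to 30% range is an assumption and is applied equally to all arms. The problem in Step 1 does not depend on it.

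**The case against.** The strongest reply is that little rests on pH. It is absent from the primary endpoint list in Section 6.6.1. Nugent score, culture and PCR are taken from all women at Visits 4 and 7, so vaginal flora is assessed without this selection. Section 14.3 rests conclusions on clinical review of descriptive summaries and urges caution in inference. All of that stands. It limits the consequence but does not supply the missing readings.

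A second reply is that pH may be routine in practice. Table 6 lists it without a condition, and Sections 9.4 and 9.7 refer swab preparation to the study manual, which is not at hand. That is possible. If so, Table 3, the Table 13 footnote and the visit text are wrong and still need correcting.

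A reader might infer four stronger things that the protocol does not support.

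- **That only symptomatic women would be tested.** Table 12 also triggers pH on examination findings and discharge, and pelvic examinations are done in all women during ring use.
- **That the table would overstate pH increases in every arm.** Indications vary, and no pH distribution for tested women is given, so the direction is unknown.
- **That testing would differ by arm because the TFV-only ring looks different.** Section 10.4 says only that site staff might work out its codes. This is a route to bias, not evidence of one.
- **That 50 planned pairs of pH values are lost.** The protocol never states a planned number of pH pairs. The 20, 20 and 10 above show only what full collection would give.

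**Conclusion.** The point holds as a contradiction between analysis and collection. Section 14.6 plans to judge treatment effects on pH, and Table 6 treats pH as a safety swab test, yet nothing in Table 3, Section 9 or Table 13 secures a pH reading from every woman after Visit 1. Followed as written, the pH shift tables would hold women selected after randomization by clinical indication and could not support a comparison between arms.

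The bias cannot be signed or sized from the protocol, and the counts in the illustration rest wholly on the assumed testing rate. The consequence is limited to the pH analysis: no listed primary endpoint is affected, and the other four variables in the sentence are collected from all women. The discrepancy is worth correcting, but it does not threaten the trial.

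**What to change.** Choose one of two changes.

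1. **Schedule it.** Record pH for every woman at Visit 4 pre-insertion and at Visit 7 pre-removal, alongside the vaginal swabs already collected. The Section 14.3 definition would then select the Visit 4 reading as baseline, close to insertion. Restrict the pH shift table to the scheduled Visit 7 reading, and list for-cause readings from other visits separately. The cost is one added reading at each of two visits. Whether an existing swab can serve, or another is needed, should be confirmed against the study manual.
2. **Drop it.** Remove pH from the shift-table sentence in Section 14.6 and list the clinically indicated values only, with visit and reason for testing. The cost is an edit to the text and the loss of a pH comparison that the present schedule could not deliver.

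In either case, bring Table 3, Table 6, the Table 13 footnote and the Section 9 visit text into agreement on whether pH is routine or conditional at each visit, including Visit 9.

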## **14.7. Evaluation of Secondary Endpoints**

### **14.7.1. Pharmacokinetic Endpoints**

After confirming that LNG and TFV levels are as expected (e.g., below level of quantification [BLQ]) for all observations from the placebo group (i.e., no previously undetected allocation errors), this group will be excluded from further PK analysis.

Plasma  $C_{\max}$ ,  $t_{\max}$  and  $AUC_{0-24h}$  (ln/linear trapezoidal method) from the intensive sampling immediately post insertion will be estimated for each participant from non-compartmental analysis using Phoenix/WinNonLin v6.1 (Pharsight, Inc., Mountain View CA) or higher. Treatment estimates for plasma  $C_{\max}$  and  $t_{\max}$  will be based on the group mean and median, respectively. Descriptive statistics of pharmacokinetic parameters will be provided by treatment group and time of measurement. Time x concentration curves associated with ring insertion will be graphed individually by participant, as well as pooled by treatment group.

To evaluate the effect, if any, of product combination,  $\log_{10}$ -transformed TFV and TFV-DP concentrations may be compared between women receiving the TFV-alone IVR vs. the TFV/LNG IVR. TFV concentrations will be compared using linear mixed models or another appropriate modeling strategy, with treatment group and center as fixed effects and time (visit) as a repeated measure. Details regarding modeling method and specification will be provided in the SAP.

Descriptive statistics and graphical displays, as needed, will also be presented by treatment group and visit for trough plasma concentrations and concentrations from other matrices (e.g., vaginal aspirate, genital tissue).

